**Figure 1 fig1:**
[figure not shown]
Flow chart for participant inclusion and follow-up: selection, inclusion, exclusion, and randomization (98).

### Participant recruitment

4.4

An open invitation will be extended to all adult women from the Huichacura-Cayuqueo Indigenous Community in the municipality of Padre Las Casas who meet the established eligibility criteria. Participant recruitment will be conducted through in-person informational meetings held at the community headquarters, complemented by digital dissemination coordinated in collaboration with the community leadership. Eligible participants will include sedentary adult Mapuche women (30, 31) with overweight or obesity and medically controlled cardiometabolic conditions, as verified through documented medical diagnoses, routine clinical follow-ups, and prescribed treatments provided by their respective primary health care centers. Participants must also demonstrate the physical ability to safely engage in moderate-intensity group exercise without assistance and have sufficient availability to attend the scheduled intervention sessions.

Individuals with medical conditions that contraindicate participation in group physical activity, including neurological events such as stroke or acute and chronic respiratory diseases, will be excluded. Detailed inclusion and exclusion criteria are presented in Table 1.

**Table 1 tab1:** Inclusion and exclusion criteria.

Inclusion criteria	Exclusion criteria
Be a woman aged 18 to 65 years.	To have organic pathologies that prevent physical activity, such as stroke, acute or chronic respiratory diseases.
Having a high level of sedentary lifestyle (more than 4 h per day) (30).	To have suffered a recent acute myocardial infarction (in the last 3 months).
To have a diagnosis of malnutrition due to overweight or obesity (based on BMI).	To have a cardiovascular pathology that prevents group physical activity.
If suffering from chronic diseases diagnosed by a doctor, such as diabetes, hypertension, or dyslipidemia, these must be properly controlled (medication use and corresponding medical checkups). with stable treatment for ≥3 months, including no recent changes in medication, no acute exacerbations, and ongoing clinical follow-up.	Having uncontrolled hypertension or diabetes mellitus, defined as lacking medical or pharmacological treatment, lacking clinical follow-up, or presenting clinical values that contraindicate participation in group exercise.
Be willing to exercise and have time available between July and September 2024 (3 sessions per week, one hour each).	Neurological, respiratory, or systemic diseases that impair the ability to perform exercise (e.g., stroke, severe chronic respiratory disease).
To have time available for an evaluation before the intervention program in July and another at the end of the program in October (each lasting approximately 2 h).	Participate in another physical exercise program during the duration of the project.
Belong to the Huichacura Cayuqueo Indigenous Community.	Use of active obesity treatments, including pharmacological therapy for weight loss (e.g., naltrexone/bupropion or agents associated with significant gastrointestinal or exercise-limiting side effects) or bariatric surgery.
Demonstrate the ability to safely perform moderate-intensity exercise, confirmed through baseline clinical screening and a submaximal 3 × 1-min step test without adverse symptoms.	Not want to participate and not sign the consent form.
Be responsible with the schedules set for the evaluation and intervention.	

### Randomization

4.5

Eligible participants will be randomly allocated to study groups following completion of baseline assessments. The randomization sequence will be generated using computer-based random number software by a co-investigator who is independent of participant recruitment and assessment procedures. Stratified randomization based on age and body weight will be applied, using permuted blocks of variable size to ensure balanced group allocation.

Allocation concealment will be maintained through the use of sequentially numbered, opaque, sealed envelopes prepared in advance by the co-investigator responsible for the randomization sequence. Envelopes will be opened only after participants have completed all baseline evaluations. Participants will then be assigned to one of two study arms: “G1” the Fit-Folk Cardiovascular Dance (FCD) group, which will receive the culturally adapted dance-based intervention, or “G2” the Conventional Physical Exercise (CPE) group, which will follow a standard exercise program.

Outcome assessors will remain blinded to group allocation. All evaluations will be conducted by personnel not involved in intervention delivery, following standardized scripts, and in separate facilities and schedules to prevent contact with intervention activities. Participants will be instructed not to disclose their group assignment during assessments. The statistical analyst will also remain blinded: an independent investigator will recode the dataset into ‘Group A’ and ‘Group B’ prior to analysis, and unblinding will occur only after completion of the primary analyses. Due to the behavioral nature of the interventions, participants cannot be blinded to their assigned program; however, this does not compromise the blinding of assessors or analysts.

### Procedure

4.6

The full study cohort will undergo in-person evaluations to assess primary and secondary outcomes two weeks before the intervention begins. Assessment appointments will be arranged through text message and subsequently verified by telephone. At the baseline visit, written informed consent will be secured, participants will be provided with hydration bottles, and a unique identification code will be assigned and documented.

During the intervention period, participant attendance will be systematically recorded, and a digital registry will be employed to document covariates that may affect outcome measures. At the conclusion of the 12-week intervention, all study variables will be re-evaluated utilizing the identical procedures (Figure 2).

**Figure 2 fig2:**
[figure not shown]
Study design of the intervention program based on culturally relevant cardiovascular dance. BMI, Body mass index; BREQ-3: Behavioral Regulation in Exercise Questionnaire-3; CONSORT: Consolidated Standards of Reporting Trials; EBS, Exercise Benefits Scale; FPT-folk: Functional progressive training with cultural significance; IPAQ-SF, International Physical Activity Questionnaire – Short Form.

All members of the technical team will participate in standardized training to guarantee uniform and impartial execution of assessment protocols. Evaluations will take place in a specially designed facility that ensures participant privacy, thermal comfort, and adequate control of lighting and ventilation. Assessments will be scheduled at consistent times of day for each participant and under conditions similar to baseline whenever possible. Participants will be directed to avoid vigorous physical activity for 24 h before the assessment, adhere to their usual diet, and ensure they are sufficiently rested. Measurements will be conducted by certified health professionals. To reduce assessment bias, outcome evaluators will maintain independence from the team implementing the intervention.

### Adverse event and safety monitoring

4.7

The intervention, which includes dance-based activities and supervised physical exercise, is categorized as minimal risk. A systematic framework will be established to monitor and document adverse events rigorously. Instructors will document instances of discomfort, minor injuries, cardiovascular symptoms, exercise intolerance, or other unforeseen events during each intervention session. All adverse events will be classified by severity and evaluated for potential correlation with the intervention, subsequently reported to the lead investigator.

Participants experiencing an adverse event will be referred to the appropriate health care facility (Servicio Alta Resolución Conunhuenu) for clinical assessment as required. Decisions about ongoing participation in the study will be determined individually, prioritizing participant safety.

To further strengthen safety procedures and in alignment with the Exercise is Medicine framework, exercise prescription will be initiated only after confirming each participant’s clinical stability and functional capacity. Training intensity and progression will be individualized according to participants’ health status and medication profiles, and instructors will continuously monitor physiological responses during sessions to minimize potential drug–exercise interactions and ensure appropriate and safe adaptation to the training program.

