##### Provider

4.9.2.2

Sessions will be conducted by a certified Fit-Folk cardiovascular dance instructor who has prior experience in implementing community-based interventions in rural regions of Padre Las Casas. The instructor will be compensated financially for professional services rendered.

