#### Provider

4.10.4

Sessions will be delivered in person by a qualified physical education professional with experience in adult fitness training.

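### The only adverse-event recording described is in-session documentation by each arm's own instructor; no uniform enquiry covers events between sessions, after absence or withdrawal, or at the final visit

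*Protocol article*

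**What the plan says.** Section 4.7 opens with a general promise: "A systematic framework will be established to monitor and document adverse events rigorously". The one collection step that follows names a recorder and an occasion: "Instructors will document instances of discomfort, minor injuries, cardiovascular symptoms, exercise intolerance, or other unforeseen events during each intervention session". The next step is processing: "All adverse events will be classified by severity and evaluated for potential correlation with the intervention, subsequently reported to the lead investigator". The section does not say who grades events or whether that person knows the allocation.

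Each arm has its own provider. For the dance arm, section 4.9.2.2 says: "Sessions will be conducted by a certified Fit-Folk cardiovascular dance instructor who has prior experience in implementing community-based interventions". For the conventional exercise arm, section 4.10.4 says: "Sessions will be delivered in person by a qualified physical education professional with experience in adult fitness training".

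For outcome assessments the plan separates measurement from delivery. Section 4.5 states: "All evaluations will be conducted by personnel not involved in intervention delivery". Sections 4.1 and 4.5 describe blinding of the outcome assessors and the statistical analyst, and 4.5 accepts that participants cannot be blinded.

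**The concern.** The safety record depends on what an instructor writes down in a session. Some problems an exercise programme can cause do not show at that moment: a joint or back complaint may be felt the next day, a symptom may occur at home, or a woman may seek care on a day without training. If she returns and mentions it, it may be recorded. If she stays away or withdraws, there is no session at which the described step can operate. Recording is then weakest among the women whose experience matters most for tolerability.

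The two recorders also differ in profession and cannot be blind to the programme they teach, and no shared wording or prompt is described. If one writes down every ache and the other only events that interrupt the class, the arms will appear to differ when they do not.

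What is at stake is the credibility of any statement that the programmes were safe or similarly tolerated. The participants are sedentary women with overweight or obesity, some with hypertension or diabetes. One arm includes loaded lifts and, where judged suitable, high-intensity intervals (4.10.3). The other progresses to modified Borg 5–9 (4.9.2.4).

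**Working it through.** There is no stated figure to reproduce, so the main check is of the text: does any other section supply a recording route that 4.7 leaves out?

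| Section | What it provides | Adverse-event route? |
|---|---|---|
| 4.6 | Attendance log; digital registry of covariates | Not described as one |
| 4.9.2.5 | Blood pressure and heart rate on site; women with diabetes report their latest home glucose reading | A pre-session enquiry, but no question on injury, other symptoms or health-care visits |
| 4.9.2.6 | WhatsApp contact, in the dance-arm section | Not described as one |
| 4.9.2.7 | Satisfaction surveys and questionnaires on behaviour change and barriers, in the dance-arm section | Not described as one |
| 4.12 | Attendance form, both arms | Shows absence, not its cause |
| 4.13–4.15 | Baseline and post-intervention measures | No adverse-event enquiry listed |
| 4.14.1 | Symptom monitoring during the step test | Covers the test only |
| 4.16 | Repeated-measures ANOVA and non-parametric alternatives | No safety analysis named |

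None of these is linked to adverse-event recording, so the in-session step in 4.7 is the only route described.

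**Who could fall outside it.** Section 4.3 adds six women to the required 16 to allow for attrition. That is 6/22 = 27% of the planned sample, so the plan itself treats loss of participants as a real possibility.

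**What differential recording could do.** Let the true risk p be the same in both arms, and let c1 and c2 be the shares of affected women whose event reaches the record. The expected recorded risk ratio is (p × c1)/(p × c2) = c1/c2. The capture shares below are assumptions, because the document gives none.

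- c1 = 50%, c2 = 50%: 0.50/0.50 = 1.0
- c1 = 80%, c2 = 50%: 0.80/0.50 = 1.6
- c1 = 90%, c2 = 30%: 0.90/0.30 = 3.0

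The first line matters: incomplete capture alone lowers the counts but does not distort the ratio. Distortion needs capture to differ by arm.

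**Scale with 11 women per arm.** If p is assumed to be 20%, the second case gives 11 × 0.20 × 0.80 = 1.76 recorded cases against 11 × 0.20 × 0.50 = 1.10, a gap of under one woman. One woman is 1/11 = 9.1 percentage points of an arm's rate, so a single unrecorded case visibly shifts a reported percentage.

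**The case against.** The strongest reply is that 4.7 is a short safety paragraph in a journal article and does not state a restrictive rule. It promises a systematic framework and then refers to all adverse events. The phrase about each session may describe when documentation takes place, which would take in discomfort a woman reports from the days before. The case report forms and the SPIRIT supplement are not shown and may hold the detail. Instructors are also the natural first recorders of what happens in class.

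Much of this stands, and it rules out several stronger readings:

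- A reader might infer that events are recorded only if they occur in a session, or that others are certainly missed. The document excludes nothing, so the supportable wording is that one route is described and other events may be missed.
- A reader might infer that a planned safety comparison is biased. Adverse events are not a listed outcome and 4.16 plans no such comparison. The concern applies only to counts that are later reported by arm.
- A reader might infer that instructor recording breaches the independence rule in 4.5. That rule concerns outcome assessors. It shows a protection that safety recording lacks, not a contradiction.
- A reader might infer that instructors rely on observation alone. The text does not say how they elicit events.
- A reader might divide session time by calendar time: 36 sessions × 1 h = 36 h of 12 × 7 × 24 = 2,016 h, or 1.8%. That is a share of time. Exercise-related events plausibly cluster in and around sessions, so it says nothing about the share of events missed.

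What the reply does not remove is that the article itself names who records and when. Even on the generous reading, a woman who has stopped attending is not reached, and no common question ties the two instructors together.

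**Conclusion.** The point holds as a weakness in the collection method that is cheap to repair. The described route depends on attendance and on a different, unblinded provider in each arm. Events outside sessions, above all those behind an absence or a withdrawal, may be under-recorded, and by-arm counts may partly reflect recording habits.

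The size of the loss cannot be estimated from the document. The ratios of 1.6 and 3.0 depend entirely on assumed capture shares, and if capture is equal in the two arms the ratio is undistorted. The conclusion also assumes that no fuller protocol or case report form already contains a between-session enquiry. If one does, it is enough to say so in 4.7. The primary outcome, estimated cardiorespiratory fitness, is measured separately and is not affected.

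**What to change.** In 4.7, add one scripted question, worded identically for both arms, about any injury, symptom or health-care visit since the last contact. Ask it:

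1. at the blood-pressure and heart-rate check that already precedes each session;
2. by phone or message after a missed session or a withdrawal;
3. at the existing post-intervention visit, preferably after the outcome measures are complete, so that an answer cannot reveal the allocation to the assessor beforehand.

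Keep the instructors' in-session record alongside it. Report events descriptively by arm and by source (in session, between sessions, after absence or withdrawal, final visit), without a formal test.

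Table 1 places the sessions between July and September 2024. If they are already complete, the article should state how events were in fact collected and limit its safety statements to what that method could detect.

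The cost is a few seconds at contacts that already take place, a short call or message to women who miss sessions, and more minor events on record. Sample size, primary analysis and visit schedule do not change.

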### Intervention

4.8

The design and reporting of the experimental and control interventions were aligned with the TIDieR guidelines to ensure transparency and reproducibility of clinical procedures (28).

### Fit-folk cardiovascular dance initiative

4.9

#### Title of the intervention and its justification

4.9.1

The experimental intervention involved a group-based Fit-Folk Cardiovascular Dance program based on Chilean and Latin American folk dances. This approach was chosen due to evidence indicating that cardiovascular dance modalities positively impact cardiovascular health (32), increase maximal oxygen uptake (VO₂max) (21), and enhance health-related quality of life (33).

#### Materials and setting

4.9.2

The intervention will require minimal equipment, including a digital blood pressure monitor and an amplified sound system. Musical selections and choreographies will be derived from Chilean and Latin American folk traditions. Sessions will be conducted at a community venue within the rural setting, offering sufficient space, a safe floor surface suitable for dynamic movement, and optional exercise mats for post-session stretching. Communication between participants and instructors will be facilitated through digital messaging platforms. No additional resistance equipment or specialized sportswear will be required.

##### Procedures

4.9.2.1

At the start of each session, participants’ blood pressure and heart rate will be measured to ensure safe participation in physical activity. Each session followed a standardized structure (Table 2). Although the intervention targets Mapuche women, traditional Mapuche ceremonial dances will not be incorporated due to their spiritual and ritual significance. Instead, Fit-Folk’s cultural adaptation is reflected in: (a) the use of folk and popular dance styles widely practiced in rural southern Chile, such as the cueca, rancheras, and cumbia, which are familiar and culturally significant to community members; and (b) the incorporation of deeply structured cultural elements, such as coordination with the Huichacura-Cayuqueo Indigenous Community, an all-female group format, culturally safe communication, and community-agreed norms. This approach ensures cultural relevance while maintaining respect for Mapuche ceremonial traditions.

**Table 2 tab2:** Structure of a Fit-Folk cardiovascular dance class.

Phase	Duration	Activity description	Intensity (Borg)	Dance styles	Country/folklore
Warm-up	8–10 min (2 to 3 songs)	Slow and progressive movements including joint mobility, basic dance steps, and dynamic stretching, aimed at increasing joint range of motion, body temperature, and cardiorespiratory activation.	Moderate, Borg 3–4	Huayno; Nicaraguan full-rhythm dances	CL and PE
Main development	35–40 min (14 to 16 songs)	The main phase of the session, characterized by higher-intensity rhythms and movements. Participants replicate Latin American folk choreographies guided by the instructor, emphasizing continuous movement and aerobic demand.	Moderate to Intense, Borg 5–9	Moderate-intensity dances: Tumbe; Afro-descendant Chilean rhythms from Arica; Colombian cumbia; Southern Chilean rancheras; Afrosaya (Bolivia); Chilean cueca. High-intensity dances: Tinkus; Forró (Brazil); Caporal; El Rin (Chile); Merengue.	BO, BR, CL, CO and PA
Cool-down/return to calm	8–10 min (2 to 3 songs)	Gradual reduction of movement intensity using slower dance steps, followed by static stretching to promote relaxation and recovery.	Low, Borg 1–3	Morenada; Venezuelan gaita; Peruvian waltz.	BO PE and VE

Borg, Borg rating of perceived exertion; BO, Bolivia; BR, Brazil; CL, Chile; CO, Colombia; PA, Panama; PE, Peru; VE, Venezuela.

##### Provider

4.9.2.2

Sessions will be conducted by a certified Fit-Folk cardiovascular dance instructor who has prior experience in implementing community-based interventions in rural regions of Padre Las Casas. The instructor will be compensated financially for professional services rendered.

##### Format and location

4.9.2.3

Intervention sessions will be conducted in person and in a group format, consisting of 11 participants per group, at the Huichacura-Cayuqueo community center, situated in the rural area where the participants reside.

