#### Title of the intervention and its justification

4.10.1

The control condition will consist of a group-based conventional physical exercise program combining resistance and cardiorespiratory training. This intervention was selected due to its documented effectiveness in improving anthropometric, metabolic, and cardiorespiratory outcomes (25, 41).

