#### Format and location

4.10.5

Group size will be consistent with the experimental condition (11 participants per group), and all sessions will be held at the Huichacura-Cayuqueo community center.

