### Statistical analysis

4.16

Multiple imputation methods will be employed to address missing data in accordance with the intention-to-treat principle (86). Descriptive statistics for continuous variables will be presented using measures of central tendency and dispersion, whereas categorical variables will be represented through frequencies and percentages. The Shapiro–Wilk test assesses data distribution, whereas Levene’s test evaluates the homogeneity of variances.

Non-parametric sensitivity analyses will be conducted when the criteria for normality or homoscedasticity are not met, due to the limited sample size (*n* = 22) and potential violations of parametric assumptions. Wilcoxon signed-rank tests will be used for within-group comparisons, while Mann–Whitney U tests will be applied for between-group comparisons.

A two-way repeated-measures analysis of variance (ANOVA) will be conducted to assess intervention effects, incorporating group (experimental vs. control), time (pre-intervention vs. post-intervention), and the group × time interaction as model factors. Bonferroni-adjusted *post hoc* tests will be utilized where necessary to determine statistically significant differences. Effect sizes will be computed utilizing Cohen’s d and classified as inconsequential (<0.20), small (0.20–0.49), moderate (0.50–0.79), or large (≥0.80) (87). Statistical analyses will be performed utilizing SPSS software (version 25; IBM Corp., Chicago, IL, USA), with a significance threshold established at *p* < 0.05. Graphical analyses will be conducted with GraphPad Prism (version 8, GraphPad Software, San Diego, CA, USA).

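### Each arm is a single exercise class, so the planned ANOVA supports a comparison of the two classes as delivered; for the programme-level claim, any positive within-class correlation pushes type I error above 5%

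*Protocol article*

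**What the plan says.** Section 4.5 of the protocol article allocates women individually. Delivery is by class. For the dance arm, section 4.9.2.3 says: "Intervention sessions will be conducted in person and in a group format, consisting of 11 participants per group". For the control arm, section 4.10.1 says: "The control condition will consist of a group-based conventional physical exercise program", and section 4.10.5 matches its size to the dance arm: "Group size will be consistent with the experimental condition (11 participants per group". Section 4.3 plans 22 women in total, 11 per arm, so one class is the whole arm.

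The providers are described in the singular. Section 4.9.2.2: "Sessions will be conducted by a certified Fit-Folk cardiovascular dance instructor". Section 4.10.4: "Sessions will be delivered in person by a qualified physical education professional".

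Section 4.16 fixes the analysis as a two-way repeated-measures ANOVA and lists its terms: "incorporating group (experimental vs. control), time (pre-intervention vs. post-intervention), and the group × time interaction as model factors". Mann-Whitney tests are named for between-group comparisons when assumptions fail. Neither has a class or instructor term.

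The Introduction (section 1) says that equal exercise dose and contact time let the trial single out culture as the main difference between arms. The research question (section 2) is put in terms of the programmes. The limitations in the Discussion (section 5) do not mention that each arm is a single class.

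**The concern.** Women who train together for 12 weeks share an instructor, a session plan and a group atmosphere. If that makes their changes more alike than the changes of women in different classes, their outcomes are not independent draws for a question about the programmes in general. Adjusting for baseline or analysing change does not remove this, because the classes form after baseline.

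The ANOVA measures the arm difference against the spread between women within a class. That spread contains nothing of the variation between classes, whereas the arm difference contains all of it. A significant result could then arise because one class or instructor happened to do better, with no difference between the programmes. At stake is whether a p-value below 0.05 may be read as evidence about Fit-Folk against conventional exercise, or only about these two classes.

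**Working it through.** **The plan's own figure.** Section 4.3 gives 16 women (8 per group) for an effect size of 0.8, 80% power and two-sided alpha of 0.05. A paired t-test with standardised change 0.8 needs 15. A group × time interaction with f = 0.8/2 = 0.4 and an assumed pre-post correlation of 0.5 reaches 80% at 16 (power 84.5%; 14 gives 78.5%). Both routes assume independent women, so the figure carries no allowance for classes.

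**Inputs.** m = 11 women per class and one class per arm (sections 4.9.2.3 and 4.10.5); m = 8 as the planned minimum (section 4.3); two-sided alpha 0.05. The ICC of change scores, ρ, is not in the document and is an assumption, shown over a range.

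**Formula.** With two time points, the group × time test equals a two-sample t-test on change scores with 2m − 2 degrees of freedom. Let σ² be the total variance of change.

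- Actual variance of the difference in class means: 2σ²[1 + (m − 1)ρ]/m.
- Variance that the t-test estimates: 2σ²(1 − ρ)/m.
- The standard error is therefore understated by the factor f = √{[1 + (m − 1)ρ]/(1 − ρ)}.
- Type I error = 2·P(t > t_crit/f).

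**Numbers for m = 11** (20 df, t_crit = 2.086):

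| ρ | f | t_crit/f | Type I error |
|---|---|---|---|
| 0 | 1.00 | 2.086 | 5.0% |
| 0.01 | √(1.10/0.99) = 1.05 | 1.98 | 6.2% |
| 0.05 | √(1.50/0.95) = 1.26 | 1.66 | 11.2% |
| 0.10 | √(2.00/0.90) = 1.49 | 1.40 | 17.7% |

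Simulation with 200,000 trials per setting gives 5.0%, 11.2% and 17.7% at ρ = 0, 0.05 and 0.10. With 8 women per class the rates at 0.01, 0.05 and 0.10 are 5.8%, 9.4% and 14.1%.

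**Negative correlation.** At ρ = −0.05 with 11 per class the rate is 0.7%, so the direction depends on the sign.

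**The same point as a fixed shift.** If the programmes are equally effective but the two classes differ by 0.5 or 0.8 SD of change, the test rejects 20% or 43% of the time.

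**Can the class variance be estimated?** Two classes minus two arms leaves 0 degrees of freedom. It cannot.

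**The case against.** The strongest reply is that women are randomised individually, so what happens in class after allocation is part of what they were allocated to. For the effect of assignment to these two programmes as delivered, the class effect belongs to the contrast and the test is not undermined. This stands. A reader might infer from the shared classes that the planned ANOVA is invalid outright, or that all its standard errors are too small. The documents do not support that: the inflation applies only when the result is carried to the programmes in general, and only if the within-class correlation is positive.

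Other points also stand in part:

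- Section 4.9.2.1 counts the all-female group format and agreed community norms as part of the cultural adaptation, and section 4.7 individualises intensity and progression. Some of what looks like class noise is programme content, and some of the shared pacing is weakened.
- One instructor per arm is inferred from singular wording. Sections 4.9.2 and 4.9.2.6 speak of instructors in the plural. One class per arm does not depend on this inference.
- Nothing in the document supports a particular ICC for change in the step-test estimate.
- Section 4.1 says a full analysis plan is public, and it is not shown here. It may discuss the matter, but it cannot estimate a variance that has no degrees of freedom, and the claim to isolate culture is in the article itself.

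**Conclusion.** The point holds in a limited form. One class per arm makes class, and apparently instructor, inseparable from arm, and the planned tests take no account of it. For the programme-level question in section 2 and the isolation claim in the Introduction, any positive within-class correlation takes the type I error above 5%. The excess is slight at an ICC of 0.01 (6.2%), more than double the nominal level at 0.05 (11.2%) and larger still at 0.10 (17.7%). These figures rest on assumed ICCs, equal classes of 11 and no programme effect. For the two classes as delivered, the planned p-value can be used as it stands. The fault is therefore the gap between what the test supports and what the article says it will show.

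**What to change.** 1. In section 4.16, state that each arm is delivered as one class, confirm whether one instructor leads each, and say that the ANOVA p-value is conditional on them.
2. Prespecify a sensitivity analysis of the primary between-arm contrast with its standard error multiplied by √{[1 + (m − 1)ICC]/(1 − ICC)}, m being the women analysed per class, for ICCs of 0.01, 0.05 and 0.10. Report whether the conclusion survives. With 11 per class, the planned t statistic would have to exceed 2.086 × 1.054 = 2.20, 2.086 × 1.257 = 2.62 and 2.086 × 1.491 = 3.11 respectively.
3. Replace the isolation claim in the Introduction with a conclusion limited to the two programmes as delivered, and name the class and instructor confounding among the limitations in section 5.

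This takes a few lines of text and a simple recalculation, with no extra participants or staff. The price is a narrower claim and wider intervals in the sensitivity analysis. That analysis shows how far the result depends on an assumed ICC; it cannot restore the 5% level.
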